# Cluster randomised controlled trial of behavioural intervention program: a study protocol for control of hypertension among teachers in schools in Kerala (CHATS-K), India

**DOI:** 10.1186/s12889-019-8082-5

**Published:** 2019-12-21

**Keywords:** Hypertension, Control of hypertension, Self-management, Intervention, School teachers, Kerala, India

## Abstract

**Background:**

Control of blood pressure among hypertensives is a major challenge around the world. Interventions for improving hypertension control in India are very limited. This paper describes the protocol for a cluster randomized controlled trial of efficacy of behavioural intervention on control of hypertension among school teachers in Kerala.

**Methods:**

A total of 92 schools are randomised to intervention and control group in Kerala. A baseline survey was conducted in all schools to assess the prevalence of hypertension and its risk factors among school teachers in Thiruvananthapuram district of Kerala state, India. Teachers in both sets of schools will receive a leaflet containing details on the importance of controlling hypertension. With the objective of improving control of hypertension, the intervention schools will additionally receive self-management education and behavioural intervention programs delivered by trained intervention managers along with measurement of weight, waist circumference and blood pressure. This intervention program will be developed based on the findings of the baseline survey and selected components of successful models of hypertension control from previous research done in similar settings. The intervention will be given for 3 months after which a post-survey will be conducted among teachers of both control and intervention schools. The primary outcome is change in control of hypertension and secondary outcome is the change in behavioural risk factors of hypertension both in the control and intervention groups.

**Discussion:**

This is the first comprehensive study looking at the efficacy of behavioural intervention on hypertension control among school teachers in Kerala, India. This study is likely to provide an upper estimate of behavioural intervention on hypertension control since teachers are reported to have one of the highest compliance rates of behavioural intervention.

**Trial registration:**

This trial was prospectively registered with the Clinical Trials Registry of India [CTRI/2018/01/011402] on 18 January 2018.

## Background

Hypertension is the major contributor to the global burden of diseases and mortality [1]. It is the most important Noncommunicable Disease (NCD) risk factor in the world as well as in India [2]. Blood pressure control among hypertensives is a major challenge around the world [3]. A comparative analysis of national surveys in 20 countries on hypertension control reported that in various parts of the world, hypertension is not adequately controlled with medication [4]. There are wide disparities in control of hypertension globally. In 2010, worldwide only 13.8% had their blood pressure controlled which was higher for high-income countries (28.4%) compared to low-income countries (7.7%) [5] In this systematic review, the United States had the highest hypertension control rate (men:48.3%, women:54.1%) whereas the corresponding figure for India was 7.3 and 7.8%. Uncontrolled hypertension is associated with high risk for development of heart disease, stroke, chronic kidney disease, retinopathy and peripheral vascular disease [6]. Implementation of innovative and cost-effective programs for control of hypertension is a major public health challenge, particularly in developing countries [5]. This could be the reason why interventions to control hypertension are limited in developing countries such as India. One such study from the Kerala state of India, the most advanced state in epidemiological transition [7], reported a four-fold increase in control of hypertension after intervention among adult hypertensives in a rural community [8]. This seven-year follow-up study reported that health promotion messages for tobacco cessation, reducing alcohol consumption, healthy eating, and physical activity was effective in control of hypertension.

Kerala state has also reported the highest prevalence of cardiovascular diseases in India [9]. Furthermore, community-based studies from Kerala reported a comparatively higher NCD risk factor prevalence [10]. Interventions among working population were found to be effective in modifying the NCD risk factors in the state [11] and other parts of India [12]. In a study from rural Kerala, 24.4% of hypertensives were aware of their condition, 19.7% were treated, and only 6.4% had their blood pressure under control [13]. The control rate is very low compared to that of high-income countries [5].Recent reports from Kerala indicated that only 13% of the hypertensive population achieved adequate control of blood pressure [systolic blood pressure (SBP) < 140 mm of Hg and diastolic blood pressure (DBP) < 90 among hypertensives] [14]. A systematic review and meta-analysis of hypertension in Indian states indicated that different states in India showed different levels of control of hypertension [15].

Teachers are role models for the community and can play a major role in school-based health education programs [16–18]. An intervention study among school teachers was reported to be effective in tobacco control in the Indian state of Bihar [19]. They can also contribute to workplace excellence and community development in society. In a highly educated state like Kerala, where access to health care is one of the best in India, there is still a lack of effective interventions for improving awareness, treatment and control of hypertension. Recent findings of a randomized controlled trial from Nepal indicated a positive effect of lifestyle intervention along with monitoring of blood pressure on reduction of blood pressure in individuals with hypertension [20]. There are many randomised controlled trials (RCT) on the effect of interventions on prevention and lowering blood pressure in India [21, 22]. A community-based cluster randomised controlled trial to improve the control of hypertension in rural India has been initiated, the outcome of which is not yet published [23]. Control of Hypertension Among Teachers in Schools in Kerala (CHATS-K) is the first comprehensive trial to evaluate the efficacy of behavioural intervention on control of hypertension among school teachers in the state. This research protocol describes the baseline survey and the plan of intervention and post-intervention study details.

## Method/design

### Study design

The study is a cluster randomised controlled trial with schools as unit of randomisation. First a baseline survey was conducted for identifying those with hypertension. After the baseline survey, the total number of schools will be randomised into two equal groups: control and intervention schools. In the intervention schools, self-management education and behavioural intervention programs will be delivered by trained intervention managers along with the measurement of weight, waist circumference and blood pressure. After 3 months of intervention, we will evaluate the control of hypertension in intervention and control groups along with other risk factors of hypertension. The study is approved by the institute ethics committee of Sree Chitra Thirunal Institute of Medical Sciences and Technology, Trivandrum, India (Reg. No 799/2015).

### Setting

The study will be conducted in the state of Kerala, which is the most advanced Indian state in terms of both epidemiological and demographic transition [7]. In Kerala, Thiruvananthapuram district was selected based on its human development index which is similar to that of the state [24] and monitoring is feasible due to its proximity to the collaborating institute.

### Participants-inclusion and exclusion criteria

Eligible schools were government or government-aided schools in Thiruvananthapuram district of Kerala state in India. Eligible participants comprised consenting male and female teachers of the selected schools, aged 30–55 years. Participants who have a fluent understanding of spoken *Malayalam* (local language) and are willing to participate in the intervention program were included. We selected teachers who have a high probability that they would be in the same school for the next year. Participant will be excluded if they do not meet any of these criteria.

### Study sample

Government or government-aided schools in Thiruvananthapuram district were identified as the primary sampling unit. The sample size for the baseline survey was 2200 teachers, expecting the prevalence of hypertension as 30% [14] to get a 95% confidence interval with an absolute precision of 2.5%, for an assumed design effect of 1.5 and non-response rate of 10%. The sample size was calculated using the Open Epi software. Among the total of 999 schools in the revenue district of Thiruvananthapuram, 902 are government or government-aided private schools. Of the 902 schools, we randomly selected 92 schools for the baseline survey using a computer-generated random assignment to get 2200 school teachers for the baseline survey (see Fig. 1). From each chosen school, we selected 15 teachers randomly if there were 15–55 teachers and for every additional 50 teachers, we selected another15 teachers. For schools with < 15 teachers, all teachers were selected. So, each cluster has approximately 15 teachers. The schools will be identified for the intervention and control by stratified randomisation with the number of hypertensives as the stratification variable.

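### The number of schools, the stated teachers per school and the total of 2200 in Study sample cannot all hold: 92 schools at about 15 each is 1380

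*Protocol article*

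**What the plan says.** All the figures stand in one paragraph, Study sample, under Method/design in the protocol article.

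- Total: "The sample size for the baseline survey was 2200 teachers". The inputs are an expected hypertension prevalence of 30%, a 95% confidence interval of plus or minus 2.5 percentage points, a design effect of 1.5 and 10% non-response.
- Clusters: "we randomly selected 92 schools for the baseline survey using a computer-generated random assignment to get 2200 school teachers". The frame is 902 government or government-aided schools.
- Draw within a school: "we selected 15 teachers randomly if there were 15–55 teachers and for every additional 50 teachers, we selected another15 teachers". Schools with fewer than 15 teachers contribute everyone.
- Summary of that rule: "So, each cluster has approximately 15 teachers".

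The article gives no distribution of school sizes and no achieved baseline count. The text states no required number of hypertensives, power or detectable difference. Figure 1 is not available to this review.

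**The concern.** A total, a number of clusters and a cluster size must multiply out, and here they do not. The gap of 820 teachers is far too large for rounding.

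Two things are at stake. First, 2200 is the only sample size in the article and the basis of the stated precision. If the cluster-size sentence is the true one, that precision is not met. Second, schools are the unit of randomisation and the trial's hypertensive teachers come from this survey, so cluster size feeds any design effect used later. A reader cannot tell whether to use 15 or 24 teachers per school.

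**Working it through.** **Inputs.** All come from Study sample: p = 0.30, d = 0.025, z = 1.96, design effect (DEFF) 1.5, non-response 10%, 92 schools, about 15 teachers per school, total 2200.

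**1. Reproduce 2200.**
- n0 = z² p(1−p)/d² = 1.96² × 0.21 / 0.025² = 1291
- × 1.5 = 1936 respondents
- / 0.90 = 2151 teachers to approach

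The stated 2200 is this figure rounded up by about 2%. At 2200 approached and 90% response (1980 respondents), the half-width is 1.96 × √(0.21 × 1.5 / 1980) = 2.47 points, so the target is met. The total is not a misprint.

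**2. Set it against the clusters.**
- 2200 / 92 = 23.9 teachers per school
- 92 × 15 = 1380, and 1380 / 2200 = 63%
- 2200 / 15 = 147 schools needed at 15 each

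Reading the 15 as respondents rather than teachers approached does not close the gap: 1936 / 92 = 21.0 respondents per school.

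**3. Can the sampling rule reach 2200?** Schools with 15 to 55 teachers give 15, smaller ones give fewer, and larger ones give another 15 for each additional 50 teachers. Starting from 15 in every school, the extra needed is (2200 − 1380) / 15 = 54.7, so about 55 blocks of 15, and more if some schools have fewer than 15 teachers. Those blocks can be spread in different ways:
- 55 schools with one extra block: 1380 + 825 = 2205
- 28 schools with two: 1380 + 840 = 2220
- 19 schools with three: 1380 + 855 = 2235

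So the rule can deliver 2200. In each case the mean is about 24, and where fewer schools supply the blocks the cluster sizes become very unequal.

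**4. Precision if about 15 is right.** Half-width = 1.96 × √(0.21 × DEFF / n).

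| DEFF | n = 1380 (all respond) | n = 1242 (90% respond) |
|---|---|---|
| 1.5 as stated | 2.96 points | 3.12 points |
| 1.31 rescaled | 2.76 points | 2.91 points |

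The second row assumes that 1.5 was set for a mean of 23.9. Then ICC = 0.5 / 22.9 = 0.022, and at 15 per school DEFF = 1 + 14 × 0.0218 = 1.31. The article states no ICC, so this is an assumption. All four values exceed 2.5.

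**The case against.** The strongest reply is that 1380 is not what the sampling rule produces. It comes only from the sentence summarising the rule. The total under the rule depends on school sizes that the article does not give, and step 3 shows that 2200 is attainable. With 19 or 28 large schools supplying the extra blocks, most schools would still draw 15 or fewer, so the sentence might loosely describe a typical school. On that reading the sample is sound and one sentence is careless. This stands as far as it goes: a shortfall is possible but not shown. It does not rescue the text, because the sentence speaks of each cluster and the mean would be about 24.

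It can also be said that baseline collection is complete, that prevalence is not the primary outcome, and that a half-width of 3.1 instead of 2.5 does little harm to a prevalence estimate. This too stands, and it limits the seriousness of the point.

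A reader might be tempted to go further in three ways that the article does not support:
- **That at least 55 of the 92 schools must have more than 55 teachers.** The count is 55 blocks, not 55 schools, because very large schools supply several.
- **That precision and headcount are both overstated by more than a third.** Only the headcount is (1380 is 37% below 2200). At the planned 90% response the interval is 16% to 25% wider than 2.5 (2.91 and 3.12).
- **That the trial comparison is underpowered.** The 2200 was sized for prevalence precision. Thirty per cent of 1980 is 594 hypertensives and 30% of 1242 is 373, but the article sets neither as a target and states no detectable difference to miss.

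**Conclusion.** The paragraph contradicts itself, and nothing elsewhere in the article resolves it. Ninety-two schools and 2200 teachers imply 23.9 per school; 92 schools at about 15 imply 1380. At least one figure is wrong, and the article does not show which.

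If about 15 is right, the planned 2.5-point half-width is missed: 2.96 to 3.12 points at the stated design effect, 2.76 to 2.91 if it is rescaled to 1.31. If 2200 is right, the precision stands at the stated design effect and the cluster-size sentence is wrong. The first branch rests on 30% prevalence, response between 90% and 100% and, for the rescaled values, an ICC of 0.022 that the article does not state.

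This should be corrected because it concerns the only stated sample size in a cluster-randomised trial. It is an error of reporting and reconciliation. It is not evidence that too few teachers were recruited.

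**What to change.** Use the baseline data, which Trial status says were complete in July 2018. State the number of teachers sampled, the number surveyed, and the mean and spread of teachers per school. Then correct whichever figure is wrong:

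- **If schools contributed about 15 each:** replace 2200 and plus or minus 2.5 points with about 1380 and about 3.0 to 3.1 points at a design effect of 1.5 (about 2.8 to 2.9 if the design effect is rescaled to about 1.31).
- **If 2200 is right:** delete "So, each cluster has approximately 15 teachers" and give a mean of about 24 with its spread.

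In either case, base any design effect on the corrected mean and spread of cluster size. The cost is a change of wording and one recalculation from data already held. Trial conduct does not change, although in the first case the stated precision becomes less favourable.

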**Fig. 1 Fig1:**
[figure not shown]
Outline of study design: enrolment, randomisation and follow up of study participants

### Baseline cross-sectional survey

A cross-sectional survey was conducted to identify school teachers with hypertension. A meeting was held with the education department, Government of Kerala to explain the study details. Office of the deputy director of education, Government of Kerala permitted to do the study and informed all the government and government-aided private schools in the selected district about the study. We then approached each of the selected school heads to get permission. From each school, teachers were selected randomly. Selected teachers were surveyed using a team of trained data collectors supervised by the research team. A brief on the study details were outlined verbally and in written format in *Malayalam* to the selected teachers before the initiation of the baseline survey. Informed written consent was obtained before the interview and measurements.

Data collection was based on an interviewer-administered survey which took approximately 30 min to complete. Additionally, physical measurements took around 15 min to complete. All assessments and data forms were checked on the day of completion. Any forms with missing data or inconsistencies were returned to the data collector for completion. Edit checks were performed and data verified as necessary.

We collected data (behavioural and anthropometric) for each participant in the selected schools using the World Health Organization (WHO) STEPS instrument for NCD risk factor surveillance. The validated standard WHO STEPS 2.1 version questionnaire was used. Baseline information on NCD behavioural risk factors was collected using WHO STEP-1, and physical measurements were done using WHO STEP-2 protocol. Blood Pressure was measured by OMRON BP apparatus (OMRON HEM-907, OMRON Healthcare Company, Kyoto, Japan). Height was measured using stadiometer, weight using SECA weighing machine and waist and hip circumference using constant tension tape using a standard protocol.

Besides, we asked questions on their morbidity pattern, cancer screening, perceptions on hypertension, opinion on the possible interventions which are likely to result in increasing control of hypertension and awareness of diabetes, hypertension and dyslipidemia status by asking questions on the history and treatment of the conditions. We also asked their knowledge about hypertension and its risk factors and their practices on healthy behaviour. The compliance to medication was also assessed using Hill-Born scale [25]. Their quality of life was assessed by the WHO quality of life questionnaire [26]. The main instruments and measurements chosen for this study are based on recommendations from the WHO STEPwise approach to NCD risk factor surveillance [27] to enable comparison of our findings to those of others.

### Outcome measurements

Prevalence, awareness, treatment and control of hypertension along with other risk factors of hypertension are collected during the baseline survey. The newly diagnosed hypertensives in the baseline survey were asked to visit their regular doctor or the nearest government primary health centre/hospital for confirmation of hypertension and management. The primary outcome of the study will be control of hypertension (defined as SBP < 140 mmHg and DBP < 90 mm [28]). This will be compared between intervention and control groups after 3 months of intervention. We will also compare the difference in mean systolic and mean diastolic blood pressure at baseline and post intervention period for control and intervention group. Secondary outcomes will be awareness and treatment rates for hypertension among teachers of intervention and control groups. We will also assess the change in risk factors of hypertension such as tobacco, alcohol, physical inactivity, unhealthy diet and, overweight/obesity after the intervention in the intervention group and the control group.

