### Plan for data collection and analysis

A follow-up survey will be conducted after the intervention to assess the change in control of hypertension, awareness and treatment for hypertension as well as other risk factors of hypertension both in control and intervention groups. Baseline survey data will be analysed to evaluate the prevalence of hypertension, and other behavioural risk factors of hypertension. Medication adherence will also be assessed. The quality of life will be analysed with hypertension status. Analysis of the opinion among school teachers regarding the feasibility of intervention options will also be done. Based on these results and already reported intervention programs in the state we will develop interventions suitable for school teachers on controlling hypertension. We will compare the control of hypertension in both study groups with the findings from baseline and post survey.

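### Newly detected and previously diagnosed hypertensives appear to share one primary control proportion, so regression to the mean will raise control in both arms and shrink the absolute difference

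*Protocol article*

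**What the plan says.** All places are in the protocol article.

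- **Identification.** *Study design*: "First a baseline survey was conducted for identifying those with hypertension". *Baseline cross-sectional survey* describes one session, with about 15 minutes of physical measurements, and no second visit before randomisation. *Control group* gives the threshold as SBP at or above 140 or DBP at or above 90 mmHg.
- **Status of the label.** *Outcome measurements*: "The newly diagnosed hypertensives in the baseline survey were asked to visit their regular doctor or the nearest government primary health centre/hospital for confirmation of" the diagnosis. *Control group* likewise has survey cases advised to re-check for confirmation. No section says that the result is recorded or that unconfirmed teachers are removed.
- **Use of the label.** The number of hypertensives is the stratification variable (*Study sample*), and the WhatsApp and SMS component goes to those identified in the survey (*Intervention components*).
- **Primary outcome.** *Outcome measurements* defines control as SBP below 140 and DBP below 90, compared between arms after 3 months. The denominator is not restated there; *Background* gives control among hypertensives.
- **Change from baseline.** The abstract frames the primary outcome as a change in control, and *Plan for data collection and analysis* says: "We will compare the control of hypertension in both study groups with the findings from baseline and post survey".
- **Data available.** *Baseline cross-sectional survey* includes questions on history and treatment of hypertension.

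**The concern.** A newly detected teacher enters the hypertensive group because a reading was high on one day, and later counts as a success if a reading falls below the same line. Blood pressure varies between visits, so some of these teachers will cross back with no change in their usual pressure. They are then scored like a treated patient at goal.

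Previously diagnosed teachers differ. Control at baseline can be measured only if known cases who read below 140/90 count as hypertensive, so as a group they are not selected on the survey reading. New cases are all uncontrolled at baseline by definition and can move only one way.

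Two things are at stake. Teachers who would read as controlled in either arm dilute the absolute between-arm difference. And a rise in control within an arm is partly statistical, which matters where the outcome is worded as change.

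**Working it through.** **1. The plan's own figure.** The only sample size shown is for the survey. *Study sample*: "The sample size for the baseline survey was 2200 teachers", "expecting the prevalence of hypertension as 30"%, "to get a 95% confidence interval with an absolute precision of 2.5"%, "for an assumed design effect of 1.5 and non-response rate of 10"%.

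- n = z²p(1−p)/d² = 1.96² × 0.30 × 0.70 / 0.025² = 1290.7
- with the design effect: 1290.7 × 1.5 = 1936
- with non-response: 1936 / 0.90 = 2152

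The stated 2200 is 2.2% higher, so it reproduces. It serves a prevalence estimate. The article shows no power calculation for the trial comparison against which dilution could be judged.

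**2. How many untreated new cases revert?** The article gives no between-visit variability, so each input here is an assumption. Three calculations:

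- *One threshold, bivariate normal.* Visit-to-visit correlation 0.6 to 0.8, and 10% to 30% of teachers above the line. P(below at visit 2 | above at visit 1) runs from 30% (correlation 0.8, 30% above) to 61% (correlation 0.6, 10% above).
- *SBP only.* Usual SBP mean 126, SD 14; within-person visit SD 7, 9 or 11 (implied correlations 196/(196 + SD²) = 0.80, 0.71, 0.62). About 36%, 43% and 48% of those at or above 140 read below 140 next time, with mean falls of 4.5, 6.8 and 9.2 mmHg.
- *The plan's rule: either pressure high to enter, both low to be controlled.* Same SBP inputs, with assumed DBP mean 78 to 82, SD 9, visit SD 5 to 7, and SBP–DBP correlation 0.7 (usual) and 0.6 (visit error). Reversion is about 32% to 44%.

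Roughly 30% to 50% is a fair working range.

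**3. Effect on the comparison.** Let u be the share of the hypertensive group that is newly detected and q the fraction of these who revert untreated. Then f = u × q reads as controlled in either arm. If p is control among the rest,

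- control in an arm = f + (1 − f)p
- between-arm difference = (1 − f)(p₁ − p₀)

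For illustration p₀ = 13%, the Kerala control rate cited in *Background*, and p₁ = 26% is an assumed doubling. The values of u are also assumed.

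| u | q | f | Control arm | Intervention arm | Difference (points) |
|---|---|---|---|---|---|
| – | – | 0 | 13.00% | 26.00% | 13.00 |
| 0.3 | 0.3 | 0.09 | 20.83% | 32.66% | 11.83 |
| 0.5 | 0.4 | 0.20 | 30.40% | 40.80% | 10.40 |
| 0.7 | 0.5 | 0.35 | 43.45% | 51.90% | 8.45 |

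**4. Effect within an arm.** New cases contribute nothing to control at baseline and u × q at the post-survey. With no effect of anything, and known cases unchanged on average, control rises by 9 to 35 points in these scenarios.

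**The case against.** The strongest points on the other side:

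- **The primary comparison is between randomised arms.** This stands. The artefact is equal in expectation in both. A reader might infer that the design invites a false positive result; it does not. Nor does any section say that a within-arm rise will be read as effect, although the wording about change leaves room for it.
- **The size is not in the article.** This stands. The survey-based starting point is "24.4% of hypertensives were aware of their condition, 19.7% were treated, and only 6.4% had their blood pressure under control", and a reader might infer from it that most survey-identified hypertensives are chance readings. The article does not support that. The figure comes from rural Kerala, not from teachers, and being unaware is not being mislabelled. Even taking 1 − 0.244 = 0.756 as newly detected with the highest SBP-only reversion of 48%, the share is 0.756 × 0.48 = 36%. A stated loss of power would need an effect size and standard error that the article does not give.
- **A single high reading is not stated.** This stands. The article cites the WHO STEP-2 protocol and gives no number of readings. Several readings at one visit would not remove variation between visits.
- **Some new cases will be confirmed and treated.** This stands, so not every later reading below 140/90 is artefact.
- **New cases are a proper target of the programme.** This also stands: they receive the messaging component, and awareness and treatment are secondary outcomes. It argues for keeping them in the analysis, not against separating them.
- **Analysis sets and subgroup tables belong in an analysis plan not shown here.** This stands in part. That new cases enter the denominator is inferred from *Background*, *Study design*, *Intervention components* and *Control group*; no section excludes them. But the entry threshold, its complement as the outcome, and the change wording are fixed in the article.

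**Conclusion.** The point holds as one of dilution and interpretation, not of validity. If newly detected teachers are in the primary denominator, as the text most naturally reads, control will rise in both arms for reasons unrelated to the programme, the absolute difference will shrink, and any within-arm change in control will be inflated.

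The direction follows from the definitions. The size does not: it rests on assumed variability (about 30% to 50% of untreated new cases reverting) and on a newly detected share that the article does not report. With an assumed share of 0.3 to 0.7, the absolute difference falls to between 91% and 65% of its undiluted value. The between-arm test remains unbiased. The comparison of mean SBP and DBP in *Outcome measurements* does not depend on crossing the threshold, although means within an arm regress too. The change below is an inexpensive improvement, not a condition for a valid trial.

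**What to change.** 1. Classify each baseline hypertensive as previously diagnosed or newly detected, using the history and treatment questions already asked before randomisation.
2. Adjust the primary between-arm comparison for this class.
3. Pre-specify the arm difference in control within each class, with the previously diagnosed as a supportive estimate.
4. Describe the overall analysis population as survey-identified hypertension.
5. State that conclusions rest on the between-arm difference and that within-arm rises in control are not evidence of effect.

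The adjustment aids precision and the class-specific estimates show the dilution. Neither removes it from the overall risk difference, and the write-up should say so.

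The cost is one baseline factor and one table, with no new data. *Trial status* places the follow-up survey in the future, so on the article's account this can be fixed before outcome data exist. The downside is that the class-specific estimates are less precise than the overall one.
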